### Labeling

All study devices will be labeled in accordance with text that is in full compliance with FDA regulations. Each study device label includes the following information:

- Protocol number
- Name and address of IP developer/distributor (Alcresta)
- Manufacturing date
- Route of administration and dosing (directed per protocol)
- Storage conditions
- Investigational device statement

## ADMINISTRATION INSTRUCTIONS AND SCHEDULE

- - - RELiZORB is intended for single-use only. At the conclusion of the feeding, the RELiZORB must be discarded. Do not store or re-use it.
    - A single RELiZORB may be used for up to 500 mL of enteral formula. For enteral formula volumes greater than 500 mL, install a new RELiZORB after 500 mL of formula has passed through the RELiZORB. A second RELiZORB may be used immediately after the first RELiZORB has been used. If less than 500 mL of enteral formula per feeding is used, the RELiZORB must be discarded after use.

Patients and patient caregivers should review the following RELiZORB installation instructions before use:

1. Set up the pump and enteral feeding pump tubing set per the pump manufacturer’s instructions. Prime the enteral feeding pump tubing per the manufacturer’s instructions.

2. Remove the RELiZORB pouch from its carton. Examine the RELiZORB pouch.

Do not use the RELiZORB if:

- the pouch seal is broken
- the current date is past the expiration date shown on the pouch

3. Remove the RELiZORB from its pouch. Examine the RELiZORB.

Do not use the RELiZORB if:

- the RELiZORB is damaged
- the RELiZORB has been previously used

4. Secure the RELiZORB to the end of the enteral feeding pump tubing set by inserting the outlet fitting from the pump tubing into the inlet of the RELiZORB with a twisting motion until secure.

5. Follow the pump manufacturer’s instructions to prime the feeding formula through to the outlet of the RELiZORB.

6. Connect the RELiZORB outlet fitting to the inlet fitting of the patient extension set or enteral feeding tube that connects to the patient.

7. If a patient extension set is being used, follow the pump manufacturer’s instructions to prime the feeding formula to the end of the patient extension set.

8. Set the pump to the prescribed flow rate between 10 and 120 mL/hr and proceed with feeding.

Feedings should be based on PI’s assessment of the patient’s daily needs and tolerance. Instructions will be provided to empty the feeding bag over a period of no more than 4 hours. The entire contents of the bag should be used to deliver the maximum dose possible. The volume of any remaining contents will be measured and recorded in the patient’s diary.

**Medication Administration:**

If medications, saline flushes or other non-enteral formula materials are to be added, they must be introduced AFTER RELiZORB (i.e. between RELiZORB and the patient). They may be added to the side-port of a Y-connector extension set located between the RELiZORB and the patient as shown below.

NOTE: If medications or flush solutions are added BEFORE the RELiZORB cartridge, then RELiZORB, all tubing and formula must be discarded. The feeding may be re-started using a new RELiZORB and patient extension set. Please follow Steps 1-7 above to re-start the process.

NOTE: If a second RELiZORB is required to be installed to replace an existing RELiZORB, use the following steps:

- Pause the pump following the pump manufacturer’s instructions
- Disconnect the current RELiZORB from the patient extension set or enteral feeding tube
- Remove the current RELiZORB from the enteral feeding pump tubing set
- Connect the new RELiZORB to the enteral feeding pump tubing set following Step 4 above
- Prime the enteral formula through to the end of the RELiZORB following Step 5 above
- Connect the new RELiZORB to the patient extension set or enteral feeding tube following Step 6 above
- Follow Step 7 above if a patient extension set is being used
- Follow Step 8 above to re-start enteral formula delivery

**Additional Information:**

- RELiZORB is for use with enteral feeding only.
- RELiZORB should not be connected to any intravenous (IV) line, set up, or system.
- Medications should not be administered through the RELiZORB cartridge. Do not add medications to the enteral feed line in between the pump and RELiZORB (before RELiZORB). The passage of medications through RELiZORB may adversely affect the medications or the ability of RELiZORB to hydrolyze fats.
- Do not re-use RELiZORB. RELiZORB is a single-use product. Re-use may result in contamination of the product. If re-used, RELiZORB may not effectively hydrolyze fats.
- Do not break, alter, or place excess pressure on any part of the RELiZORB cartridge. Any compromise of the structural integrity of RELiZORB may lead to improper connection to enteral feeding pump tubing sets and patient extension sets or enteral feeding tubes, enteral formula leakage or risk of contamination.
- Do not use RELiZORB after the date marked on the pouch.
- Enteral formulas containing insoluble fiber should NOT be used. Insoluble fiber may clog the RELiZORB cartridge. A detailed listing of enteral formulas compatible with RELiZORB can be found at www.relizorb.com/formulas.
- RELiZORB is designed for use with enteral feeding pump systems with low flow/no flow alarms. RELiZORB is NOT intended for use with gravity feed systems. A detailed listing of pumps, enteral feeding pump tubing sets and patient extension sets or enteral feeding tubes compatible with RELiZORB can be found at www.relizorb.com/pumps. RELiZORB has been evaluated with enteral pump flow rates between 10 and 120 mL/hr.
- Up to 2 RELiZORBs can be used in a day (24-hour period) and there are no requirements on the amount of time between using them

Further details on dosing instructions and schedule can be found in the Study Procedures Manual.

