| This clinical trial includes an initial screening visit (Day -3) in which subjects will be screened for eligibility, including baseline clinical and physical assessments. At screening the investigator or designee will review the subject’s medical history to determine eligibility, explain the study to the subject and the subject’s parent or legal guardian, and if eligible, obtain informed consent. If consent is given and the subject is deemed eligible based on the results of the screening visit, they will be enrolled in the study and pre-baseline assessments will be performed, which will include physical examination, nutritional assessment, vital signs, 72-hour fecal stool collection, and clinical evaluations.  Treatment will be administered on study Day 1, followed by daily use of the RELiZORB enzyme cartridge whenever enteral nutrition is administered, for a total of 90 days. During the treatment period, all enteral nutrition will be administered through the RELiZORB enzyme cartridge. Nutritional intake (24-hour enteral dietary and PN volume intake), stool consistency/amount/frequency (if applicable) or ostomy (if applicable) output, study device use, and incidence of symptom changes will be recorded daily electronically or on paper by the subject’s parent or guardian. Throughout the duration of the study, parents or guardians will also be contacted daily by a study coordinator and/or dietician to assess nutritional record and identify any other potential problems. Clinic visits will occur on Days 7, 14, 28, 60, and 90 (range ± 3 days) of the treatment period. Assessments for the primary endpoint and safety will be collected during these visits and through a weekly phone call with at-home weight measurement using a standardized scale. Advancement of oral or enteral feedings and weaning from parenteral feeding will be determined by the investigator during the weekly phone calls and scheduled clinic visits based on the subject’s clinical status, which will include assessment of weight, growth and hydration status. | |
| **Number of subjects (planned):** A total of 32 pediatric subjects with SBS, aged 2 years -18 years, are expected to be enrolled in the study over a period of 48 months. | |

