| The investigator will assess the subject’s nutritional intake, weight, height, and hydration status to determine if, based on their medical judgment, changes to the subject’s nutritional treatment should be made.  The subject’s parent or guardian will be given access to an electronic diary(or given a paper diary if no electronic capability) and instructed to record daily any changes in symptoms (e.g., abdominal pain, increases in stool output above baseline, stool consistency through Bristol scale), stool amount/frequency (if applicable), ostomy (if applicable) output and use of the study device. The subject’s parent or guardian will be instructed on how to administer enteral nutrition using the RELiZORB enzyme cartridge and will be provided with RELiZORB enzyme cartridges to take home. The subject’s parent or guardian will also receive education from a registered dietician on recording caloric intake and composition in oral and enteral feeds, and TPN. As part of this education, the subject’s parent or guardian will receive access to a nutrition/food tracking phone application (Cronometer) to assist them in this task throughout the study.  The subject’s parent or guardian will then be asked to collect all stool for 72-hours over study Day -3 to Day -1 and to record caloric intake and composition in oral and enteral feeds, and TPN during that time. This will be used to determine the baseline coefficient of fat absorption.  The first enteral feeding with the RELiZORB enzyme cartridge will occur under the observation of a member of the research team (Day 1). The parent or guardian will supply and prepare the enteral formula. The feeding regimen, including type of formula, will not be changed for research purposes. Subjects will remain on their current regimen. Additionally, only standard (non-blenderized) commercial formulas will be permitted to be used with the RELiZORB enzyme cartridge. Amino-acid based formulas that are compatible with the RELiZORB enzyme cartridge will be permitted based on the inclusion criterion requiring formulas be compatible with the device prior to study enrollment.  Any Adverse Events (AEs) that occur after the use of RELiZORB enzyme cartridge will be recorded according to the procedures described below. Any significant clinical finding prior to use of the study device will be included in the subject’s medical history.  **Treatment Period (Day 1 to 90)**  During the treatment period (Day 1-90) all enteral nutrition via pump (tube feeds) will be administered through a RELiZORB enzyme cartridge. RELiZORB is a single-use product and a new device will be used with each new enteral feeding period. Re-use may result in contamination of the product. If re-used, RELiZORB may not effectively hydrolyze fats.  The subject’s parent or guardian will record daily the use of the device, the subject’s nutritional intake (24 hour oral and enteral intake and PN volume) and any changes, stool consistency (Bristol scale)/amount/frequency (if applicable), ostomy (if applicable) output, ,any changes in symptoms (e.g., abdominal pain, increases in stool output above baseline), and urine color using an a nutrition phone application and electronic diary (or using a paper diary if no electronic capability) . Access to a nutrition/food tracking phone application along with a daily phone call from a study coordinator will be used to ensure accurate recording and completion of these tasks. In addition, if the subject experiences any unexpected physical or medical condition, or an in-hospital admission, the subject’s parent or guardian will be directed to call the clinic immediately and report it to the study staff.  Subjects will return to the clinic on Day 7, Day 14, Day 28, Day 60, and Day 90 of the treatment period. The final clinic visit will be preceded by a repeat 72-hour stool collection for fat analysis. During the clinic visits, staff will review the information in the subject’s diary, review compliance with the use of the study device and discuss relevant observations with the subject during the visit. Information contained in the diary will be entered in the electronic database in a timely manner. In addition to a daily study coordinator phone call, the study staff will have weekly telephone contact with families during interim weeks after the day 14 visit. Study staff will monitor safety, diaries, weekly weights, stool composition (Bristol scale) and output, changes in caloric intake, changes in urine output, and will make adjustments to PN and enteral feeding accordingly. Adjustments will be based on the subject’s nutritional needs, weight, height, hydration status and investigator’s medical judgement. If necessary, unscheduled visits can be arranged in place of the telephone contacts.  At each clinic visit, vital signs, physical examination, clinical evaluations, adverse events, concomitant medications, medical/surgical procedures, and blood tests to determine the levels of liver enzymes will be performed. Blood samples will also be collected to analyze lipid profiles. All AEs post-baseline that occur will be recorded. Participants will meet with a study dietician during each clinic visit to assess nutritional needs and address issues or concerns. | |

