### Inclusion Criteria

To be considered eligible to participate in this study, a subject must meet all the inclusion criteria listed below:

1. Male or female patients, aged 2 years – 18 years, inclusively.
2. Diagnosed with SBS, as determined by medical history and PN dependence (i.e. need for PN for >60 days after intestinal resection or a bowel length <25% of expected).
3. Congenital or acquired gastrointestinal disease requiring surgical intervention that has occurred at least 3 months prior to screening.
4. Patient is on parenteral lipid and at least 30% of daily caloric and fluid intake has been provided by PN for at least 6 months prior to screening.
5. Stable PN nutrition requirement, determined by less than 5% reduction in PN nutrition for at least 1 month prior to screening, or at the discretion of the investigator.
6. The patient has a Central Venous Catheter (CVC) at the time of study inclusion.
7. Screening direct bilirubin that is in the normal range for age or is not determined to be clinically significant by the investigator.
8. The patient has an existing feeding tube, receiving enteral nutrition via an enteral feeding pump at a rate>10ml/hr but <120ml/hr, and is able to tolerate at least 10 ml/kg/day enteral nutrition with which the RELiZORB cartridge can be used.
9. Stable enteral nutrition requirement with no change in formula composition or rate for at least 1 month prior to screening.
10. The patient or a parent or legal guardian of the patient is able to read, understand, and is willing to provide informed consent (or assent, if applicable) for the patient.
11. The patient (if assent is applicable) or a parent or legal guardian is able to understand the requirements of the study and is willing to bring the patient to all clinic visits and complete all study related procedures (as determined by the investigator).
12. A parent or legal guardian is willing to provide written authorization for the use and disclosure of protected health information.

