## COMPLIANCE WITH INVESTIGATIONAL PRODUCT

The subject’s parent or guardian will be required to document the subject’s daily nutritional intake (24 hour oral and enteral caloric intake/composition and PN volume) using an electronic phone-based application (Cronometer; or paper diary if there is no electronic capability). The study device use and incidence of any changes in symptoms (e.g., abdominal pain, increases in stool output above baseline) will be recorded using the electronic diary (or paper diary). The subject’s parent or guardian will receive education and continued support from a study dietician to assist them in keeping track of nutritional and total caloric intake, as well as caloric composition in the diary throughout the duration of the study. Access to the electronic nutrition application (Cronometer) will facilitate this recording. The first and final clinic visits will be preceded by a required 72-hour stool collection for fat analysis.

The study staff will review the diaries and question the subject or the subject’s parent or guardian about protocol compliance at the clinic and weekly telephone visits. For hospitalized subjects, compliance will be assessed through daily monitoring of nutritional markers and review of medication administration records which utilize point of care bar code technology. Details of the study device use will be recorded on the CRF.

In the event that an out-of-state study patient is hospitalized at a hospital other than Boston Children’s and to ensure patients are able to remain in the study at an outside institution, at the time the patients are enrolled in the study, they will be provided a copy of their signed consent and the study protocol with study team contact information with instructions to bring these materials, along with the supply of RELiZORB devices, to the hospital so that they can use them in the event of an inpatient admission.

If a subject fails to comply with protocol requirements, the subject may be discontinued from the study. Compliance will be considered to have been achieved if the subject receives ≥80% of the planned enteral nutrition using the device.

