During the treatment period, all enteral nutrition will be administered using the RELiZORB enzyme cartridge. Nutritional intake and composition (24 hour oral and enteral intake and PN volume) will be recorded on the phone based application (Cronometer; or paper). Stool consistency (assessed through the Bristol scale), stool amount/frequency (if applicable) or ostomy output (if applicable), study device use, and incidence of any changes in symptoms (e.g., abdominal pain, increases in stool output above baseline, change in urine color/frequency) will be recorded by the subject’s parent or guardian in their electronic or paper diary. After the daily phone call with a study coordinator, the coordinator will email the study team list serve to address any issues or concerns as these occur. Advancement of oral or enteral feedings and weaning from PN feeding will be determined by the investigator weekly and at each clinic visit based on the subject’s clinical status, which will include assessment of weight, growth and hydration status. Assessments for the study endpoints and safety will be collected at clinic visits, by physical examination, clinical evaluations and review of the subject’s diary. Assessments will also occur at interim weekly telephone visits after the Day 14 clinic visit as above.

A complete overview of the time and events schedule of this study is presented in Table 2.

Table 2. Schedule of Time and Events

|  | **Study Period** | | | | | | | | |
| --- | --- | --- | --- | --- | --- | --- | --- | --- | --- |
|  |  | | **Treatment Period** | | | | | | |
| **Measurements/Evaluations** | **Screen-**  **ing**  **Day -3** | **Enroll-ment**  **Days**  **-3 to -1** | **Baseline and first treatment**  **Day 1** | **Day**  **2-6** | **Day 7±3** | **Day**  **8-13** | **Day 14±3** | **Day**  **15-27**  **Day**  **29-59**  **Day**  **61-89** | **Day**  **28±3**  **Day**  **60±3**  **Day**  **90±3** |
| I/E criteria | X |  |  |  |  |  |  |  |  |
| Informed consent | X |  |  |  |  |  |  |  |  |
| Demographics | X |  |  |  |  |  |  |  |  |
| Bowel length^a^ | X |  |  |  |  |  |  |  |  |
| Standard of care | X | Daily | X | Daily | X | Daily | X | Daily | X |
| Medical history | X |  |  |  |  |  |  |  |  |
| Vital signs^b^ | X |  | X |  | X |  | X |  | X |
| Anthropometry/Physical exam^c^ | X |  | X |  | X |  | X |  | X |
| Study Coordinator Call |  | Daily |  | Daily |  | Daily |  | Daily |  |

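### The cartridge limits cap device-treated formula at 1,000 mL/day, so the rule that all enteral nutrition goes through the device, and above 1,250 mL/day the 80% compliance rule, cannot be met by every eligible child

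*Protocol*

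**What the plan says.** **Device limits.** Section 4.2 states "A single RELiZORB may be used for up to 500 mL of enteral formula", and its additional information adds "Up to 2 RELiZORBs can be used in a day (24-hour period". Section 4.2 also says that a cartridge is discarded once a feeding ends, even if less than 500 mL was given. The synopsis (Treatment Period) calls for a fresh device at every new feeding period.

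**Required share.** The synopsis says "all enteral nutrition via pump (tube feeds) will be administered through a RELiZORB enzyme cartridge". Section 6.1 says "During the treatment period, all enteral nutrition will be administered using the RELiZORB enzyme cartridge", and the synopsis methodology and duration paragraphs say the same.

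**Compliance.** Section 4.4 says "Compliance will be considered to have been achieved if the subject receives ≥80% of the planned enteral nutrition using the device". Section 10.2.4 repeats the threshold and excludes subjects below it from the per-protocol population, which is used for sensitivity analysis. The primary efficacy population is the full-analysis set, which keeps subjects whatever their compliance. Sections 4.4 and 9.12.3 allow a subject to be discontinued for not complying with the protocol.

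**Eligibility.** Section 3.2.1 requires a child to be "receiving enteral nutrition via an enteral feeding pump at a rate>10ml/hr but <120ml/hr" and to tolerate at least 10 mL/kg/day. Parenteral nutrition (PN) must have supplied at least 30% of daily calories and fluid. No maximum daily enteral volume is given.

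**The concern.** Each rule is reasonable alone, but together they cannot all be followed once a child's planned tube-feed volume is large enough. Staff and families would then have to break a stated rule, and the protocol does not say which one gives way or how the excess formula is counted.

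For the analysis, a child could be recorded as non-compliant because of a device ceiling rather than anything the family did. The reported compliance percentage would mix the two causes. The per-protocol set would lose cap-limited children along with non-adherent ones. Because enteral advancement and PN weaning are managed together, and PN calories are the primary outcome, some of those losses could be related to progress on treatment.

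**Working it through.** The protocol states no daily device capacity, so there is no figure of its own to reproduce. The inputs are 500 mL per cartridge and 2 cartridges per 24 h (Section 4.2), the 80% threshold (Sections 4.4 and 10.2.4), pump rates above 10 and below 120 mL/h and the 30% PN minimum (Section 3.2.1), and maintenance fluids from Table 3 (Section 7.1.5).

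**1. Capacity.** 2 × 500 = 1,000 mL/day.

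**2. Volume above which each rule fails.**
- All enteral nutrition through the device: above 1,000 mL/day.
- 80% rule: above 1,000 / 0.80 = 1,250 mL/day.

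**3. Pump rates that give these volumes.**

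| Volume | Over 24 h | Over 12 h |
|---|---|---|
| 1,000 mL | 1,000/24 = 42 mL/h | 1,000/12 = 83 mL/h |
| 1,250 mL | 1,250/24 = 52 mL/h | 1,250/12 = 104 mL/h |

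All four rates lie inside the entry range.

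**4. Highest attainable compliance** at planned volume V is min(1, 1,000/V): 91% at 1,100 mL, 80% at 1,250 mL, 67% at 1,500 mL and 50% at 2,000 mL.

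**5. Split feeds.** If the synopsis means one cartridge per feed, k equal feeds a day give at most min(1, 2/k). Three feeds give 67% and four give 50%, at any volume.

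**6. Which children (illustration).** Assume total fluid equals Table 3 maintenance, which above 20 kg is 1,500 mL plus 20 mL for each kg over 20, and that the tube supplies the full 70% not given by PN.
- 1,250 / 0.70 = 1,786 mL, and 20 + (1,786 − 1,500)/20 = about 34 kg.
- 1,000 / 0.70 = 1,429 mL, which the 10 to 20 kg row of Table 3 reaches at 10 + (1,429 − 1,000)/50 = about 19 kg.
- With a 50% tube share the weights are 45 kg for 1,000 mL and 70 kg for 1,250 mL.

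**7. Advancing feeds.** The protocol does not say whether the 80% is judged daily or over the study. With linear advancement and compliance pooled over 90 days:

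| Planned volume, start to end (mL/day) | Highest pooled compliance |
|---|---|
| 500 to 1,000 | 100% |
| 800 to 1,200 | 95% |
| 800 to 1,600 | 81% |
| 1,000 to 1,500 | 80% |
| 1,000 to 1,800 | 71% |

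For 800 to 1,600, a quarter of the days average 900 mL and the rest are held at 1,000 mL, so the treated mean is about 975 against a planned mean of 1,200. In the 39 of 90 days when planned volume exceeds 1,250 mL, the same child would fail a daily rule.

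**The case against.** The strongest reply concerns scale.

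**Volume at entry.** With at least 30% of fluid from PN, tube plus oral intake is at most 70% at entry. A reader might infer from the pump-rate ceiling that volumes near 2.8 L/day (119 × 24 = 2,856 mL) are ordinary. They are not: that volume implies total fluid of at least 2,856 / 0.70 = 4,080 mL/day, which Table 3 reaches at about 149 kg. Continuous feeding at 80 or 100 mL/h likewise corresponds to about 82 and 116 kg. Table 3 gives maintenance fluid only and the PN criterion applies at entry only, so these are not hard limits, but they are corner cases. This objection stands.

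**Advancement.** A reader might also infer that children fail by succeeding. The pooled figures do not support this: doubling from 800 to 1,600 mL/day still gives 81%. Absolute volume decides the result, and oral advancement does not count towards it. Some children who advance past the limit are affected, but advancement alone does not cause failure.

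**Bag time.** Section 4.2 says "Instructions will be provided to empty the feeding bag over a period of no more than 4 hours". It would be tempting to conclude that two cartridges cover only 8 hours. The section does not equate a bag with a feeding, and it allows a second cartridge straight after the first, so that conclusion is not supported.

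**Consequence.** The full-analysis set is primary and keeps these children. This also stands.

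**Study Procedures Manual.** Section 4.2 refers further dosing detail to this manual, which is not at hand. It may explain practice, but it would not remove the conflict within the protocol's own text.

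**Conclusion.** The conflict is real and follows from the protocol's own figures. Device-treated formula is capped at 1,000 mL/day, so the requirement to pass all enteral nutrition through the device cannot be met above that volume. The 80% rule cannot be met above 1,250 mL/day. Between the two volumes only the first requirement is broken. If one cartridge per feed is meant, the 80% rule also fails with three or more equal feeds a day, whatever the volume.

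The likely cases are larger children with a high tube-fed share, from about 34 kg for the 80% rule under the illustrative 70% assumption. The number affected cannot be computed, because the protocol gives no distribution of enteral volumes.

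The primary analysis is not affected. The consequences are limited to the reported compliance percentage, the per-protocol sensitivity set and possible discontinuation for non-compliance. A reader might infer that the per-protocol set will systematically lose the children whose feeds advanced most. The document shows that this could happen to some, not that it will in general.

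**What to change.** Reconcile the synopsis (methodology, duration of treatment and treatment period) and Sections 4.2, 4.4, 6.1 and 10.2.4 with the eligibility criteria. Either the cartridge limit, the all-enteral-nutrition requirement and the 80% rule should be such that every eligible child can meet all three, or the protocol should state how formula beyond the limit is given and counted. The same amendment should make clear whether a new device is needed for each feed and over what period the 80% is judged. Which limit holds is for the sponsor-investigator and the manufacturer.

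In the analysis:
- report the share of total daily enteral volume that passed through the cartridge as an exposure measure;
- count subjects below 80% because of the cartridge limit separately from those below 80% through non-adherence;
- show the per-protocol sensitivity analysis with and without the cap-limited subjects.

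Simply changing the denominator of the 80% rule to the volume that the limit allows is not recommended as the sole remedy. A child on 2,000 mL/day with half the feed untreated would score 100% and stay in the per-protocol set, mixing full and half exposure.

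The cost is amendment wording, one extra sensitivity run and possibly one diary field. Intake, device use and leftover bag volume are already recorded, but the protocol does not say that volume given without the cartridge is.
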